## Abstract

**Introduction:**

The rising prevalence of knee osteoarthritis is placing a considerable strain on the global healthcare system. To address this issue, telemedicine-supported multicomponent exercise therapy has emerged as a promising approach. This therapy combines exercise, patient education, and health coaching to empower knee osteoarthritis patients to manage their condition from the comfort of their homes. Nevertheless, there are some existing limitations in the current research on this approach, including challenges related to patient compliance and the absence of objective evaluation methods.

**Methods and analysis:**

Patients diagnosed with knee osteoarthritis, who have not undergone knee surgery in the past year, will be recruited for a randomized controlled trial. The trial will include an intervention group and a control group. The intervention group will receive an mHealth app-based multicomponent exercise therapy, consisting of exercise therapy, patient education, and health coaching. Meanwhile, the control group will receive usual care, involving drug therapy and patient education. The primary outcome of the trial will be the measurement of pain intensity, assessed using a visual analog scale at baseline and at 4, 8, and 12 weeks of the post-intervention. To analyze the data, a two-factor, four-level repeated measures ANOVA will be used if the assumptions of homogeneity of variance and sphericity are met. If not, a mixed effects model will be employed.

**Discussion:**

The aim of the study is to evaluate the effectiveness of multicomponent exercise therapy aimed at enhancing pain self-management for knee osteoarthritis patients in the comfort of their own homes. The intervention incorporate wearable devices equipped with advanced deep learning systems to monitor patients' adherence to the prescribed at-home exercise regimen, as well as to track changes in outcomes before and after the exercise sessions. The findings from this trial have the potential to enhance both the accessibility and quality of care provided to knee osteoarthritis patients, offering valuable insights for future improvements in their treatment and management.

**Trial registration:**

Chinese Clinical Trials Registry, ChiCTR2300073688. Registered on 19 July 2023, https://www.chictr.org.cn/bin/project/edit?pid=199707. World Health Organization International Clinical Trials Registry Platform, https://trialsearch.who.int/Trial2.aspx?TrialID=ChiCTR2300073688.

**Supplementary Information:**

The online version contains supplementary material available at 10.1186/s13063-023-07749-4.

## Introduction {6a}

Knee Osteoarthritis (KOA) is a prevalent global disability disease and represents the most common form of arthritis. Individuals living with KOA often endure symptoms such as pain, swelling, and stiffness around the knee, primarily caused by the degradation of articular cartilage or injury to the subchondral bone [1]. The worldwide impact of KOA is substantial, affecting over 260 million people, with a notable increase of 9.3% between 1990 and 2017 [2]. It is estimated that radiographically confirmed symptomatic KOA accounts for 3.8% of all KOA cases, with the prevalence escalating with age, surpassing 10% among individuals aged 60 and above [3]. This upward trend in KOA prevalence is projected to persist due to aging populations and the growing rates of obesity, placing a significant burden on society. A key objective in the treatment of knee osteoarthritis (KOA) is the reduction of pain and improvement of functioning. To address these goals, treatment approaches should target factors contributing to pain and physical function. Guidelines recommend first-line treatments such as exercise, education, weight loss, health coaching, self-management, and psychosocial support [4–6]. Studies have demonstrated that multicomponent exercise therapy provides greater benefits to KOA patients compared to single physical therapy interventions [7, 8]. This comprehensive approach addresses the dysfunction and mental health of KOA patients from a socio-biologic-psychological perspective, resulting in improvements in peripheral muscle strength, joint motion, and central motor control. Additionally, health coaching plays a significant role in changing patients' pain perception and reducing fear of exercise. By offering an effective means for KOA patients to enhance their quality of life and reintegrate into society, this multi-modal therapy holds promise for improved outcomes [9, 10].

Despite the strong recommendation for multicomponent exercise therapy in the guidelines for knee osteoarthritis (KOA) management, its widespread implementation faces challenges due to limited consultation time and the labor-intensive nature of the approach. KOA is a chronic musculoskeletal pain syndrome that necessitates long-term treatment. However, practical limitations such as geographical barriers, transportation issues, and time constraints often result in patients having to self-manage their condition at home [11]. The advent of telemedicine has presented an opportunity to enhance the utilization of multicomponent exercise therapy for the home-based self-management of knee osteoarthritis (KOA) patients. Telemedicine, a component of telehealth, involves the use of software-based, evidence-informed approaches for disease treatment, management, or prevention [12]. By harnessing the power of the internet, mobile devices, smartphones, websites, and other technologies, telemedicine can be utilized either independently or in conjunction with other therapies such as medications or medical devices to optimize patient care and improve outcomes. Accumulated evidence suggests that telemedicine holds the potential to improve treatment efficiency, overcome geographical barriers, reduce costs, and mitigate exercise-related injuries when conducted in the home setting [13, 14]. Based on our analysis of 20 randomized controlled trials, we found that telehealth-supported exercise programs resulted in significant improvements in pain and disability among knee osteoarthritis (KOA) patients [15]. As a result, the demand for telemedicine advice and interventions has witnessed a substantial increase [16]. However, it is important to acknowledge that older KOA patients may encounter challenges in utilizing telemedicine, such as difficulties in app registration and website logins. Additionally, telemedicine relies on remote monitoring, which means that patients receive follow-up care at home. This can limit outcome assessments to subjective measures like questionnaires, potentially introducing bias into the results [17]. Furthermore, ensuring compliance with exercise prescriptions is essential for the success of multicomponent exercise therapy, but currently, there is a lack of standardized objective tools to assess compliance.

Telemedicine holds promise in enabling multicomponent exercise therapy for knee osteoarthritis (KOA) patients at home. However, it is crucial to consider the specific requirements of older patients and the limitations associated with objective outcome measurement. To strengthen telemedicine-supported exercise programs for KOA, it is important to develop tools that can objectively monitor exercise compliance. Considering this, we have designed a randomized controlled trial that integrates telemedicine and exercise therapy for KOA patients using a user-friendly mobile app and wearable devices to track home-based exercises. The mobile app features a simple interface that is easy to use for individuals from diverse backgrounds. The app will record exercise duration and login times, providing an objective measure of patients' exercise compliance. Furthermore, the wearable devices will monitor joint movement during exercise, ensuring that the prescribed exercises are performed correctly and enabling quantitative evaluation of compliance. This trial aims to compare the outcomes of telemedicine-supported multicomponent exercise therapy (the trial group or TG) with usual care (the control group or CG). The primary goal is to assess whether the trial group exhibits better outcomes in terms of reducing the need for clinical care, decreasing pain levels, and alleviating activity limitations in KOA patients after they have completed standard conservative treatment.

## Methods

### Primary objective {7}

The primary objective of this study is to assess the effect of telemedicine-supported multicomponent exercise therapy on pain management in patients with knee osteoarthritis in comparison to usual care therapy.

### Secondary objectives {7}

i)Evaluate the effects of telemedicine-supported multicomponent exercise therapy on physical function and quality of life in knee osteoarthritis patients compared to usual care.ii)Assess the impact of multicomponent exercise therapy on self-cognition, mental health status, and the reduction of pain fear and pain catastrophic imagery in patients with knee osteoarthritis.iii)Determine the level of adherence to multicomponent exercise therapy among KOA patients who self-manage their condition at home. 

### Design {8}

This study is a randomized controlled trial with two parallel groups, conducted in an open-label, difference-test manner, following a 1:1 allocation ratio, within a single center over a span of 12 weeks. Patients afflicted with knee osteoarthritis, visiting the outpatient physiotherapy clinic, will be extended an invitation to partake in the study. Post-eligibility screening, participants will be randomly assigned to either the treatment or control group. The trial aims to enroll 86 subjects. The study protocol will be articulated in accordance with the Standard Protocol Items: Recommendations for Interventional Trials (SPIRIT) guidelines [18]. A completed SPIRIT checklist can be located in Additional File 1.

### Participant timeline {13}

This study will commence with the eligibility screening of prospective participants. Those meeting the eligibility criteria will be enrolled in the study and briefed on the procedures entailed. Participants deemed eligible and willing will be required to provide written informed consent (accessible in Additional File 2) prior to enrollment. We will assess their outcomes at the outset (W0), following 4 weeks of treatment (W5), 8 weeks of treatment (W9), and 12 weeks of treatment (W13). The schematic diagram illustrating the participant timeline is depicted in Fig. 1.

**Fig. 1 Fig1:**
[figure not shown]
The schematic diagram of the participant timeline

### Setting {9}

The study will begin recruiting participants in July 2023. Data collection and intervention administration are expected to conclude in July 2024. Participants will be recruited through Room 902, Special Needs Outpatient Department of West China Hospital, Sichuan University, Wuhou District, Chengdu City, Sichuan Province, China.

### Eligibility criteria {10]

If a patient expresses interest in participating, researchers will evaluate their eligibility based on the study's inclusion and exclusion criteria (Table 1).

**Table 1 Tab1:** Inclusion and exclusion criteria

Inclusion criteria	Exclusion criteria
18 years old or older	Knee arthroscopy or open surgery in the past 12 months, elective knee replacement
Clinical signs and symptoms corresponding to KOA, according to the 2021 COA guidelines	With other joint problems (such as severe osteoporosis, rheumatoid arthritis, fracture, gout, joint tuberculosis, or joint tumor)
Kellgren-Lawrence Grade I–III of KOA	Malignant illness or other major conditions (e.g., unstable cardiovascular disorders or lung disease, dementia) that restrict the ability to adhere to the recommended treatment
Visual analog scale (VAS) score ≥ 4 points [19]	Cognitive impairment resulting in the inability to understand the physical therapist’s instructions and the content in the app
Access to smartphone or tablet	Pregnant women
Participate in the experiment voluntarily and sign the informed consent	The supervision and care of other family members cannot be guaranteed for each exercise training
Accept randomization assignment	Neurological disorders
Candidates who meet all the above criteria will be included	Candidates meeting any of the above criteria will be excluded

### Recruitment {15}

Participants for the trial will be recruited from Room 902, Special Needs Outpatient Department at West China Hospital, Sichuan University. Individuals meeting the eligibility criteria will be briefed on the trial procedure, following which, upon signing the informed consent form, they will be enrolled in the study. Those not meeting the eligibility criteria will be directed to the standard treatment protocol as per their preference. To reach the desired sample size, we will administer unified training and supervision to researchers to enhance the success rate of securing informed consent during interviews. Concurrently, we will employ other effective recruitment strategies, such as referrals from medical examination centers or relevant departments, and poster campaigns, to robustly ensure a swift recruitment pace of participants.

### Consent {26a}

A physical therapist will assess individuals who meet the aforementioned prerequisites to determine their eligibility for participation in the study. Initial study information outlining the trial’s background, appropriate population, interventions, risks and benefits of participating, along with rights and responsibilities, will be shared with potential participants by both physicians and researchers. Upon agreement to participate, individuals will receive detailed written information elucidating the study’s objectives and methodologies, and they will be required to sign three informed consent forms. One copy will be retained by the participants, another will be electronically scanned by the physiotherapist during the initial visit, while the third copy will be securely stored by the Ethics Committee of Sichuan University. The informed consent will be signed and obtained on the day of the first visit at Room 902, Special Needs Clinic, West China Hospital, Sichuan University.

### Additional consent provisions for collection and use of participant data and biological specimens {26b}

There are no additional biological samples to be collected.

### Randomization and blinding

#### Sequence generation {16a}

Block randomization with a computer-generated random sequence will be utilized to conduct randomization as participants are recruited. A designated data manager, who is not involved in recruitment, intervention, or evaluation processes, will be assigned to generate random sequences and store them securely in IBM SPSS, version 26.0.1.

Furthermore, the randomization list will be securely stored both digitally within a password-protected database, and physically in a secure, locked location within our facility. Only authorized personnel, such as the designated data manager and the principal investigator, will have access to the randomization list, ensuring its integrity throughout the course of the study. This setup not only safeguards the list but also allows for a structured protocol that remains unaffected by individual personnel changes.

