#### Concealment mechanism {16b}

An independent researcher, not involved in the experiment, will follow the computer-generated random sequence results to insert the assignment codes into sequentially numbered, sealed, opaque envelopes, thereby obfuscating group allocation. As per the experimental design, once opened according to the stipulated procedures, participants will be assigned to either the “control group” or “trial group” based on the corresponding “0” or “1” on the random number card.

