#### Implementation {16c}

During the recruitment phase, participants will be evaluated by a physical therapist who is not involved in the randomization process. Following this evaluation, sealed and opaque envelopes will be opened on-site to ascertain the assignment group, with participants thereafter being allocated to the respective groups in a 1:1 ratio. To ensure a balanced distribution among the groups, permuted blocks of size 4 will be employed randomly.

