### Blinding

#### Who will be blinded {17a}

Blinding of volunteers and doctors to group assignments is unfeasible. The decision not to blind the assessors is made given that the subjects are not blinded and the outcomes are self-reported. Although participants, doctors, and assessors are not blinded, alternative methods are employed to minimize bias. Specifically, participants and assessors are not informed of the trial hypothesis to mitigate the risk of bias stemming from unblinding.

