#### Composition of the coordinating center and trial steering committee {5d}

A group of individuals oversees this trial, including a principal investigator who is in charge of both the prosecution and medical treatment of the participants, two data managers who ensure data capture and quality, a study coordinator who manages registration and study visits, and a study physician who selects potential participants and oversees proper follow-up. Every Monday, the team meets; however, neither the trial steering committee nor a stakeholder/public involvement group are present.

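### Allocation concealment is weakened: the principal investigator, who is in charge of participants' treatment, may read the randomisation list during enrolment, and the only block size stated is 4 in an open-label, single-centre trial

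*Protocol article*

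**What the plan says.** All references are to the protocol article.

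- **Who sees the list.** Sequence generation {16a} states: "Only authorized personnel, such as the designated data manager and the principal investigator, will have access to the randomization list". The words introducing the two roles present them as examples, so the set of readers is not closed. The same sentence describes the arrangement as "ensuring its integrity throughout the course of the study", and nothing defers access until enrolment has ended.
- **Who the principal investigator is.** Composition of the coordinating center and trial steering committee {5d} lists "a principal investigator who is in charge of both the prosecution and medical treatment of the participants".
- **How assignments are generated.** Implementation {16c} says that "permuted blocks of size 4 will be employed randomly". No other size is named and no stratification is mentioned.
- **Setting.** Design {8} describes a trial "conducted in an open-label, difference-test manner, following a 1:1 allocation ratio, within a single center over a span of 12 weeks". Who will be blinded {17a} adds: "Blinding of volunteers and doctors to group assignments is unfeasible".
- **Safeguards.** Concealment mechanism {16b} has a researcher from outside the experiment put the codes into "sequentially numbered, sealed, opaque envelopes". Under Implementation {16c}, a physical therapist with no part in randomisation first evaluates the participant. After that, "sealed and opaque envelopes will be opened on-site to ascertain the assignment group". The data manager who generates the sequence has no recruitment, intervention or evaluation role {16a}. A study physician, listed separately from the principal investigator, selects potential participants {5d}.

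**The concern.** Concealment protects enrolment only if nobody who can influence it knows the next assignment. There are two separate weaknesses here.

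The first is list access. The protocol requires the data manager to be independent of recruitment, intervention and evaluation. It then gives the same list to a role that it ties to participants' treatment. An opaque envelope hides nothing from someone who can look up its contents.

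The second is predictability. In an open-label trial at one center, past allocations are visible to staff. If they also know that every four consecutive patients split two and two, some later assignments follow from earlier ones without any list.

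What is at stake is selection bias: eligibility judgements, effort in seeking consent, or timing of enrolment could come to depend on the coming arm. There is room for this. Entry requires a self-rated pain score above a threshold (Table 1), and Recruitment {15} treats success in obtaining consent as something that staff can raise. The mitigation named in {17a}, withholding the trial hypothesis from participants and assessors, does not bear on who is enrolled. Reporting bias from an unblinded, self-rated outcome is a different problem, which concealment would not solve.

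**Working it through.** **Inputs.** 86 participants and 1:1 allocation (Design {8}); block size 4 (Implementation {16c}). The 86 is used only as the number of assignments. It reproduces from Sample size calculation {14}: 64 / (1 − 0.25) = 85.3, rounded up to 86.

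**List holder.** Every assignment is known, 86 of 86, whatever the block size.

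**Observer without the list.** Assume that this person knows the block size and follows all allocations in order. A 2:2 block of 4 has 6 equally likely arrangements.

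| Position in block | Probability it is certain in advance | Probability the best guess is right |
|---|---|---|
| 1 | 0 | 1/2 |
| 2 | 0 | 2/3 |
| 3 | 1/3 (first two alike) | 1/3 × 1 + 2/3 × 1/2 = 2/3 |
| 4 | 1 | 1 |
| Sum per block | 4/3 | 17/6 = 2.83 |

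- Complete blocks: (4/3) / 4 = 33% certain; 2.83 / 4 = 70.8% guessed correctly.
- 86 = 21 × 4 + 2, so there are 21 complete blocks and two further patients.
- Certain in advance: 21 × 4/3 = 28 of 86 (32.6%). The last two positions add none.
- Guessed correctly: 21 × 17/6 + 1/2 + 2/3 = 60.7 of 86 = 70.5%, against 50% if nothing could be predicted.

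**Effect of varying the block size.** The sizes are illustrative and not from the protocol. They are drawn with equal probability, and the observer knows the possible sizes but not which one is in use. Results are from 400 simulated sequences of 86.

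| Sequence | Certain in advance | Best guess right |
|---|---|---|
| Fixed 4 (exact) | 32.6% | 70.5% |
| 4 or 6 | 5.8% | 69.1% |
| 4, 6 or 8 | 2.0% | 67.9% |

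The same simulation with fixed blocks of 4 returned 32.7% and 70.5%, in line with the exact values. Repeat simulations for sizes 4, 6 and 8 gave up to 2.3% certain, so about 2% is the figure to use. Varying sizes nearly removes certainty but lowers guessing accuracy by less than three percentage points (70.5 − 67.9 = 2.6).

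**Roles side by side.** The data manager has the list and is expressly excluded from recruitment, intervention and evaluation. The principal investigator has the list, is in charge of treatment, and is not excluded from recruitment anywhere. The evaluating physical therapist and the selecting study physician are not named as having the list, but the people overseeing the trial, including the principal investigator and the study physician, meet every Monday {5d}.

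**The case against.** The strongest answer is that the protocol separates the roles that matter. An independent person generates the sequence and an outside researcher fills the envelopes. A therapist outside the randomisation process evaluates patients, and a study physician selects them. Being in charge of treatment may mean oversight only, since Interventions assigns treatment in both groups to qualified physiotherapists. A breach through the list would need the principal investigator to influence selection or pass information on. All of this stands, and it limits the conclusion. It does not remove the weakness, because no section bars the principal investigator from recruitment. Concealment should not depend on a list holder's silence.

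On block size, a fixed block of 4 is a common choice and contradicts nothing in the protocol. The prediction figures also assume staff who know the size and track allocations in order, which the document does not state. That stands too. It makes the block size the lesser part of the point, as does the small fall in guessing accuracy when sizes vary.

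A reader might infer that concealment fails outright and that any upcoming assignment can be known. The documents do not support this: only a list holder could know every assignment, about two thirds are not determined for anyone else, and no breach is described.

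**Conclusion.** Allocation concealment is compromised by arrangements that the protocol states, but it is not shown to fail. The firmer part is list access: a role in charge of treatment can read all 86 assignments during enrolment, and the envelopes give no protection against that. This rests only on {16a} and {5d}, and on the absence of any rule that keeps the role out of recruitment.

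The second part is conditional. If staff know the block size and track allocations in order, about one third of assignments (28 of 86) are certain in advance, with 70.5% guessed correctly. The wording that blocks are used randomly is unclear, but with one size given a fixed block of 4 is the fair reading.

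It would also be wrong to infer that varying the block size restores concealment. It leaves the list holder's knowledge untouched. No sample-size figure changes. The point should be corrected, and the cost is administrative.

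**What to change.** 1. **Main change.** In {16a}, name the people who may read the list and, until enrolment closes, limit them to persons with no recruitment, treatment or assessment role: the data manager who generates it and one independent back-up custodian. The back-up meets the stated aim of withstanding personnel changes. The principal investigator's access is withdrawn until then. The cost is a change of access rights and one revised sentence.
2. **Secondary change.** For patients not yet randomised, have the data manager generate a new sequence with randomly varying block sizes (for example 4, 6 and 8), and keep the sizes from recruiting staff. The cost is a new list, a new set of envelopes, and a possible final imbalance of a few patients. Stopping inside a block of 8 can leave the arms up to 4 apart; the current plan already ends inside a block of 4, where the gap can be 2.

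The second change does not replace the first.
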